### Interventions

#### Scheme of standard analgesic use

The scheme of standard analgesics used for each participant includes two parts. First, patient-controlled analgesia (PCA) will be used from the day of surgery to the postoperative day (POD) 3, and in the meanwhile, flurbiprofen axetil (100 mg) by intravenous drip is to be administered twice a day. Second, during the POD 4 to POD 14, the participants will only intake etocoxib orally, 60 mg qid.

All participants can ask for additional analgesia if necessary. The additional consumption of analgesia (type and dosage) will be recorded daily and finally statistically analyzed.

#### TEAS interventions

TEAS will be performed using XCH-C1 equipment (ShangHai Nuo Cheng Co.). Based on the theory of Traditional Chinese Medicine, two circular electrodes (2 cm × 2 cm) will be placed around the surgical knee acupoints of SP9 (YINLINGQUAN) and GB34 (YANGLINGQUAN). SP9 is located at the hollow between the inferior edge of the medial tibial condyle and the medial edge of the tibia. GB34 is located at the lateral side of the calf in the hollow, anterior and inferior to the fibular head [31]. Before electrode attachment, E will shave and sterilize the skin with 75% ethyl alcohol. The TEAS produces a balanced, asymmetrical biphasic waveform with a pulse width of 200 μs, and a strong but comfortable current amplitude [32]. Intervention duration will be set as 30 min per day for 2 weeks [33]. Participants will be required not to change the current settings by themselves during the application of TEAS. A 30-min TEAS will be daily applied prior to a 30-min rehabilitation (including flexibility, strength, range of motion, balance and gait exercises [34]).

For the active TEAS (5 Hz/100 Hz/mixed) group, a continuous frequency of 5 Hz/100 Hz/mixed will be used. The placebo group will deliver a strong but comfortable current for 30 s which then gradually vanishes over the next 15 s. One study [35] has demonstrated that this new sham device can promote the effect of blinding through eliminating expectation bias and clarifying the true efficacy of TEAS. In this way, a sound emitted at the end of TEAS will indicate the endpoint of the TEAS treatment, which achieves the best blinding effect on participants and the outcomes assessor. Meanwhile, the participant will be told that: the TEAS works all the time during its application and they may or may not experience sensations from the TEAS unit due to different sensation thresholds of different people.

### Outcomes evaluations

Pain intensity (rest and movement) and the American Knee Society Score (AKSS) are the primary outcomes. Secondary outcomes include active range of motion (AROM) of the knee that was operated on, surface electromyography of both quadriceps, the modified 30-s sit to stand test, additional use of analgesics and the 36-item Short Form health survey (SF-36). The additional outcomes include patient satisfaction rate, patient expectation rate and the incidence of analgesia-related side effects.

The pain intensity, AROM, incidences of analgesia-related and TEAS-related side effects will be daily recorded. Evaluation of the patient satisfaction rate and patient expectation rate will be conducted after the first episode of the TEAS intervention. The SF-36 will be evaluated at two time points: before the TEAS intervention, and 2 weeks after the TEAS intervention. The assessment time points of the remaining outcomes are before the surgery, after the surgery before the TEAS intervention(at POD 3), and 1 week and 2 weeks after the TEAS intervention.

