### Randomisation and allocation concealment

Participants who meet the screening criteria will be randomized into four balanced groups: G1, G2, G3 and G4. The randomization sequence will be computer-generated by an independent research staff (C) with a 1:1:1:1 ratio using SPSS 21.0.

At POD 3 and before the TEAS application, three physical therapists (D, E, F) will be mainly responsible for the treatment sessions and outcomes evaluation. Initially, D will perform the basic measurements of participants in four groups and double-check whether the sensation in the leg that was operated on is normal. After D leaves the ward, E will apply a 30-min TEAS intervention and subsequently F will perform a 30-min rehabilitation session per day in four groups. One TEAS intervention and one rehabilitation constitute one treatment session. Immediately after the end of one treatment session, D will return to the ward, evaluate and record the outcomes according to the trial design. Researchers except for C and E will be blinded to the treatment allocation. Randomisation and allocation concealment in a light-tight sealed envelope until E firstly reveals the TEAS intervention according to the random number sequence at POD 3. Participants will be required not to communicate with any other researchers, participants and care providers to minimize the risk of potential bias. After the latest TEAS intervention, participants and outcome assessors will be asked to guess whether the subjects received active TEAS or placebo TEAS within 5 min to evaluate the blinding quality.

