### The additional outcomes

Both physical factors and psychological factors contribute to dissatisfaction [46]. Hence, the patient satisfaction rate or expectation rate will be used to control the psychological factors. Participants will be asked to rank their satisfaction with a 5-point scale (1 = very unsatisfactory; 2 = unsatisfactory; 3 = neutral; 4 = satisfactory; 5 = very satisfactory), and the frequency of the “very satisfactory” determines the satisfactory ratio [47]. Patient’s expectation rating is ranked with 3-point scale (1 = positive; 2 = neutral; 3 = negative). The incidence of side effects of analgesia (nausea/vomiting/dizziness/sleepiness) and the TEAS (local irritation, redness, contact dermatitis, or muscle ache) will be recorded daily.

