### Statistical analysis

All data will be analyzed using the statistical package for IBM SPSS Statistics V21. The intention-to-treat (ITT) and per-protocol sets (PP) will be analyzed. Continuous data are presented as mean ± standard deviation (SD), and categorical variables are described as percentages. Baseline data will be collected and analyzed. Continuous data with normal distribution and homogeneity variance will be analyzed using analysis of variance (ANOVA). Otherwise, the Kruskal-Wallis *H* test will be performed.

Statistical analysis includes the following four aspects. Firstly, the repeated measurement data will be analyzed using the mixed-effects model or generalized estimating equation (GEE) or generalized linear mixed models (GLMMs). Secondly, the correlation between different outcomes will be analyzed using the multiple linear regression or logistic regression. In this study, NRS, sEMG or AROM are independent variables, whereas the AKSS or m30STS test are dependent variables. Psychological factors serve as covariance. Thirdly, the safety analysis of TEAS will be compared between groups using *χ*^2^ test or Fisher’s exact test. Fourthly, health economic evaluation (cost-effectiveness analysis) will be performed. A *P* value < 0.05 (two-side) is considered statistically significant.

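### Expectation and satisfaction are rated only after the first TEAS session but used as control covariates, so they can already depend on allocation and early pain relief

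*Protocol article*

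**What the plan says.** **Timing.** Under Outcomes evaluations the article states: "Evaluation of the patient satisfaction rate and patient expectation rate will be conducted after the first episode of the TEAS intervention". The same paragraph gives separate schedules for the daily measures and for SF-36, and assigns the remaining outcomes to visits before surgery, at POD 3 before TEAS, and at weeks 1 and 2. The text therefore gives the two ratings a single time point and no pre-treatment value.

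**Role as control variables.** Under The additional outcomes: "the patient satisfaction rate or expectation rate will be used to control the psychological factors". Under Statistical analysis: "Psychological factors serve as covariance". That sentence closes the second of four analysis aspects, in which "the correlation between different outcomes will be analyzed using the multiple linear regression or logistic regression", with NRS, sEMG or AROM as predictors and AKSS or m30STS as the response. The first aspect, the repeated-measures model (mixed model, GEE or GLMM), names no covariates.

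**Role as outcomes.** "The additional outcomes include patient satisfaction rate, patient expectation rate and the incidence of analgesia-related side effects".

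**What precedes the ratings.** Allocation stays concealed "until E firstly reveals the TEAS intervention according to the random number sequence at POD 3". Active sessions run for 30 minutes. For the sham, "The placebo group will deliver a strong but comfortable current for 30 s which then gradually vanishes over the next 15 s".

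**The concern.** A covariate meant to remove the influence of patients' prior psychology should be fixed before treatment can act on it. Here both ratings come after randomisation and after a first exposure that differs between arms in what the patient feels. A patient's expectation or satisfaction at that point may partly be a response to the device or to early pain relief.

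Two things are at stake.

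- **The stated regression.** If the rating partly records early relief, holding it fixed removes some of the association between pain and function that the regression is meant to describe. Because allocation and early pain can both feed into the rating, conditioning on it can also create associations that were not there.
- **The satisfaction outcome.** Treatment is daily for 2 weeks, but the only rating stated follows the first session. The mixed arm alternates 5 Hz and 100 Hz by day (abstract; Discussion), so a mixed-arm patient has by then received only one of the two frequencies. That rating cannot distinguish the mixed regimen from a single-frequency one, although the mixed regimen is the subject of the trial's hypothesis.

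**Working it through.** The plan gives no figure for this point, so the check is mainly a reading of the text, followed by a conditional illustration.

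**1. Order of events**

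| Step | Section |
|---|---|
| Assessor takes baseline measures at POD 3, before TEAS | Randomisation and allocation concealment |
| Envelope opened, first TEAS session given | Randomisation and allocation concealment |
| Active: 30 min of current; placebo: 30 s + 15 s = 45 s | TEAS interventions |
| Expectation and satisfaction rated | Outcomes evaluations |
| Ratings used as psychological covariates | The additional outcomes; Statistical analysis |

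The ratings follow both randomisation and exposure.

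**2. The model in which the covariate is placed**

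With standardised variables, response A (AKSS or m30STS), predictor N (for example NRS) and rating M, the adjusted coefficient of N in a linear regression is

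(r_AN − r_AM · r_NM) / (1 − r_NM²).

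It differs from the unadjusted r_AN in general when M is correlated with N. If M were a pre-treatment trait, that change would be the purpose of adjustment. If M partly results from early relief or from allocation, the change mixes control with removal of the signal. The documents give none of the three correlations, so neither size nor direction can be stated.

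**3. Illustration if the ratings entered a model containing treatment group**

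Inputs from Sample size: difference 2, SD 2.88, 33 per group, two-sided α 0.05, 80% power. These reproduce: 2 × (1.960 + 0.842)² × 2.88² / 2² = 32.6, so 33; and 33 × 4 / 0.85 = 155.3, so 156. Power at 33 per group is 80.5%.

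Assumptions not in the documents: treatment shifts the rating by g SD; the within-arm correlation of rating and pain is r; the whole rating–pain slope is causal. The slope is b = r × 2.88, which is 0.86 for r = 0.3 and 1.44 for r = 0.5. The adjusted effect is 2 − g·b. Its standard error is √(2.88² − b²) / √(66 × 0.25 × (1 − ρ²)), with ρ² = 0.25g² / (0.25g² + 1).

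| g | r | Removed, g·b | Adjusted effect | Share removed | Approx. power |
|---|---|---|---|---|---|
| 0 | 0.3 / 0.5 | 0 / 0 | 2.00 / 2.00 | 0% / 0% | 84% / 90% |
| 0.3 | 0.3 / 0.5 | 0.26 / 0.43 | 1.74 / 1.57 | 13% / 22% | 72% / 71% |
| 0.5 | 0.3 / 0.5 | 0.43 / 0.72 | 1.57 / 1.28 | 22% / 36% | 61% / 52% |
| 0.8 | 0.3 / 0.5 | 0.69 / 1.15 | 1.31 / 0.85 | 35% / 58% | 44% / 25% |

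A binary version gives the same order of size. If 70% of active and 40% of placebo patients rate expectation positive, and a positive rating goes with 0.75 to 1.5 NRS points less pain, then 0.30 × 0.75 = 0.23 to 0.30 × 1.5 = 0.45 points are removed, or 11% to 23% of 2. Varying the split from 60/50 to 80/30 gives 0.10 × 0.75 = 0.08 to 0.50 × 1.5 = 0.75 points, or 4% to 38%.

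With no shift between arms (g = 0) nothing is lost and precision improves.

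**The case against.** **The covariate is not in the group comparison.** A reader might infer that the primary treatment effect on pain will be biased. The document does not support that. The covariate sentence belongs to the between-outcomes regression, where NRS is a predictor and no group term is named, and the repeated-measures model lists no covariates. The sentence under The additional outcomes about controlling psychological factors is general, so it leaves the possibility open but does not commit the trial to it. This objection stands and limits the point.

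**The sham is built to prevent a shift.** It starts with the same sensation, ends with a sound, and comes with a script saying that sensations may or may not be felt. It is therefore too strong to say that treatment has already changed the ratings. The text supports only that it can have done so.

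**The attenuation figures reflect assumed inputs.** This is correct. They apply to a model that the plan does not specify and say nothing about the AKSS or m30STS regression.

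**Satisfaction is a minor outcome and may be rated more than once.** The article does not say whether it refers to TEAS, analgesia or surgery, and the schedule figure is not shown, so further time points cannot be ruled out. The text, however, states only one. First episode could also be read as the whole 2-week course, but the section on randomisation uses TEAS intervention for a single 30-minute application. On the other reading the complaint about satisfaction timing falls, while the ratings remain post-treatment covariates.

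**It may be too late.** Recruitment was planned for May 2018 to May 2019 and the article is dated 29 May 2019. Moving the question may help few or no patients, which is why the fix includes an analysis-only fallback.

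**Conclusion.** The point holds in a limited form. The plan fixes post-exposure ratings as control covariates and also lists them as outcomes. That choice can distort the planned regression of AKSS or m30STS on NRS, sEMG or AROM, by an amount the documents do not allow one to compute.

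Bias in the treatment effect arises only if the ratings are added to the repeated-measures group model and treatment has in fact shifted them. Under the assumed shifts of 0.3 to 0.5 SD and correlations of 0.3 to 0.5, the loss would be about 0.26 to 0.72 of 2 points. This is a warning against that extension, not an estimate of error in the plan as written.

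The satisfaction point does not depend on any model. On the natural reading of the text, one rating after session 1 cannot represent 2 weeks of treatment or the mixed regimen. The sample size of 156 is unaffected. The change is worth making because it corrects a stated rule at little cost.

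**What to change.** 1. Ask the 3-point expectation item at the POD 3 baseline, before the first TEAS session, when the assessor already takes baseline measures. Use only that value as the psychological covariate.
2. Treat satisfaction as an outcome only, repeat the 5-point question at the existing week-2 assessment, and never enter it as a covariate.
3. State in the analysis section that ratings taken after the first session are not added to the group-comparison model.
4. For patients already treated, omit the post-session ratings from adjusted models and report them descriptively by arm.

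Cost: one question moved, one question repeated at an existing visit, and no change to sample size or treatment. The real loss is that expectation cannot be adjusted for in patients already treated. If recruitment has closed, only items 3 and 4 remain possible, together with the week-2 satisfaction question for anyone still on treatment.

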#### Demographic and medical variables

Preoperative demographic information includes sex, age, height, weight, duration of KOA, type and duration of complication, marital status, occupation, racial background, education level, preoperative medication and history of major operations.

#### Pain intensity (resting and movement)

Pain intensity is usually measured based on an 11-point Numerical Rating Scale (0–10 NRS) [36, 37]. The NRS is a horizontal line marked with the numbers 0–10 at equal intervals where 0 indicates “no pain” and 10 indicates “worst pain imaginable.” The NRS is the preferred intensity scale rather than Verbal Descriptor Scale, and Visual Analog Scale with a lower error rate and standard validity [38]. Most importantly, attributes of the NRS are not related to patient age.

Pain intensity evaluation will be carried out at rest and with movement. Prior to other procedures, the pain intensity at rest is evaluated in a position where the participant lies comfortably and still. The pain intensity at the maximum active flexion of the knee that was operated on is recorded as the pain intensity with movement.

#### The American Knee Society Score (AKSS)

The AKSS is commonly used for outcomes evaluation after the TKA globally [39], including knee assessment (0–100) and functional assessment (0–100), a total of 200 points [40]. The knee assessment consist of three components: pain (0–50), range of motion (0–25) and stability (0–25). Deduction is determined by the presence and severity of flexion contracture (0–15), extension lag (EL, 0–15) and malalignment (0–20). Function is evaluated via walking (0–50) and climbing stairs (0–50) with deductions for walking aid (0–20). For each part, a negative score is possible and should be transformed to zero.

The knee stability evaluation consists of two parts: the anterior-posterior stability test and the lateral stability test. The procedure of the anterior-posterior stability test is the same as that of the anterior drawer test of the knee. During the lateral stability test, the surgical knee is flexed by 30°. The participant will be required to stand when measuring the lower extremity alignment, and the acute angle between two lines (anterior superior iliac spine to the midpoint of the knee, the midpoint of the knee to the midpoint of the ankle) will be recorded. Valgus of 5–10° is considered to be the normal alignment and three scores are deducted for each degree of malalignment outside this range [41]. For measuring EL, a towel roll will be placed under the heel of the knee that was operated on. The participant will be required to extend their knee as much as possible, and keep the knee as straight as possible to raise the lower extremity off the towel roll. The physical therapist keeps the goniometer in alignment to measure the degrees from the straight position. The number of degrees is subtracted from the knee extension AROM to obtain the degrees of EL [42].

#### AROM measurement of the operated knee

In order to reduce the measurement error to the greatest extent, the knee AROM will be measured using a standard goniometer by the same physical therapist [43]. Bone marks of the great trochanter, the lateral epicondyle of the femur and the lateral malleolus will be firstly identified. The axis of the goniometer is positioned over the center of the lateral epicondyle of the femur. The distal arm is aligned with the fibula using the lateral malleolus and the proximal fixed arm is aligned with the femur using the greater trochanter. During the measurement, the participants will be asked to flex or extend the knee that was operated on to the maximal extent of pain that they could tolerate. Supine position is adopted for measuring the knee AROM. During the measurement of the AROM of knee flexion, participants will be required to slide the heel towards the buttocks by themselves to the greatest extent possible. When measuring the measurement of the operated knee (AROM) of knee extension, participants will be asked to extend the knee where a towel roll is placed under the heel as straight as possible. A positive value indicates a flexion position when the initial position of the knee is at the maximum extension position. AROM will be measured in triplicate for calculating the average AROM value.

#### Modified 30-s sit to stand (m30STS) test

The m30STS test will be conducted to assess the physical performance of the elderly, ensuring that people with lower body functions can also complete the test [44].

Before the m30STS test, the evaluator should first clearly introduce it to the participants. A trial is needed prior to the real test. The participant will be required to sit in the middle of the standard armchair (17 in. in height and 18 in. in width), back straight, feet shoulder-width apart, and placed on the floor at an angle slightly back from the knee. Instructions to the participate are: “When I say ‘1, 2, 3 start’, you stand up and then sit down again with both your lower limbs together as much as possible. Try your best to stand up and sit down as many times as possible until the end of 30 s. You can use your hands to help you stand up or sit down if necessary, and I will stand by your side to protect you.” The evaluator will record the number of STS repetitions.

#### Surface electromyographic (sEMG) of both quadriceps

Surface EMG will be measured simultaneously with the m30STS test. The sEMG data will be collected using a TeleMyo 2400 wireless sEMG tester (Noraxon, USA) for three major muscles of both leg: vastus medialis (VM), rectus femoris (RF) and vastus lateralis (VL), with six tunnels in total, and 1500 Hz of the sampling frequency. The electrode is a disposable ECG electrode (Ag/Cl, T-800).

Participants will be requested to wear loose pants to expose the thigh prior to sEMG. For securing the quality of the sEMG signal, the evaluator should shave the skin, sterilized with 75% alcohol and allow it to evaporate before attachment of the electrodes. Bipolar electrodes must be placed parallel to the estimated longitudinal axis of the muscle fibers below, including RF (the midpoint between the anterior superior iliac spine and the upper margin of the patella), VM (the evaluator places a towel roll under the non-surgical knee’s popliteal fossa and asks the participant to extend the knee to press the towel roll forcefully, then the bulging area slightly proximal and medial to the patella is the muscle belly of VM. Since the quadriceps of the knee that was operated on after surgery are so weak making finding the muscle belly difficult, the same area of the non-surgical knee symmetrical to the operated one, therefore, will be selected to perform the test) and VL (the midpoint between the greater trochanter and the inferior margin of the patella). The center-to-center electrode distance is 2 cm. The reference electrode is placed over the fibula head. For fastening the electrodes, the evaluator will use athletic tape for adding security without additional pressure on the top of the electrodes. Finally, fastening the wires against the body will prevent the electrodes from being pulled off, but the wires will not be placed in a way that alters the movement patterns of the participants.

A pressure transducer, instead of a high-speed camera, will be used to objectively identify the time point. The seventh tunnel (the type of tunnel is “test TTL”) will be connected to the FSR400 force-sensitive resistance transducer (the sensitivity ranges from 0 to 10 kg) to measure the change of the buttocks’ pressure during the m30STS test. The pressure signals can be transported simultaneously to the computer by a mainboard (Arduino UNO). The start time point of standing up (t1) and the end time point of sitting down (t2) will be precisely identified once the pressure value is obtained by the A0 port (range 0–1023) of mainboard exceeds 200. Data exported will be analyzed by Matlab programming. Firstly, the sEMG signals exported in the middle three STS repetitions will be denoised using a 10–400-Hz bandpass filter. The duration (t2–t1) of one STS test will be standardized by unifying interpolation of 10,000 data points. Root mean square (RMS), peak value and integrated EMG (iEMG) will be finally calculated after duration standardization. Each index will be tested three times to record the average value for statistic analysis. An engineer blinded to treatment allocation will conduct a sEMG analysis.

